#### Measures

##### Primary outcome

Our primary outcome is the time to onset of depression or anxiety disorders in the offspring, based on the Child version of **Diagnostic Interview Schedule for Children** Version IV NIMH DISC-IV; [40], which is a highly structured diagnostic assessment instrument designed to gather symptom presence for child and adolescent psychiatric disorders based on the symptoms and criteria variables as defined in the Diagnostic and Statistical Manual of Mental Disorders DSM-IV; [41]. The computerized DISC is administered via a computer (the interviewer reads questions from the computer screen and enters responses directly into the computer) and scored by computer algorithm [42]. There are parallel versions of the instrument: the DISC-P for parents, and the DISC-C for direct administration to children. In the present study the DISC-C is used to assess anxiety disorders and depression, and a brief assessment of alcohol and drug use. The DISC-P is used as a parent report of children’s anxiety and depression symptoms as well as questions about whole life symptomatology. At the 12- and 24-follow-up assessments, the interviewer addresses the past 12 months. If any disorder was present, the interviewer makes an estimation of the time of onset and the duration of the disorder. The interviewer combines information retrieved from the DISC with the **Weekly Emotions Diary for Youth (WEDY;** [name] & [name], Weekly Emotions Diary, unpublished manuscript**)** as input. All children included in the intervention trial are asked to keep a weekly diary during the study, giving scores of three items: anxiety, sad mood, and happiness on a 0–5 scale. This chart was developed for the purpose of the current study, primarily as a helpful tool to obtain a good estimate of the onset and duration of a disorder (if present by DISC-criteria), since children may not always have an adequate sense of time when retrospectively reporting over the past year. Children are encouraged to fill out the diaries either on paper or through the internet in a web-based diary. They receive an incentive of 1 euro per month for completing the weekly diary, with a maximum of 25 euros.

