### Participants

Participants in the study are children of patients with and anxiety or mood disorder. We aim at screening 554 children (T0), and at including 204 children in the intervention phase of the study. We have designed in- and exclusion criteria for parents and children:

Inclusion criteria (parents):

At least one of the biological parents, currently or in the past five years, treated for a unipolar mood disorder or an anxiety disorder; informed consent.

Exclusion criteria (both parents):

Mental retardation; severe alcohol or substance use disorder; schizophrenia or other primary psychotic disorder; schizoaffective disorder; bipolar disorder.

Inclusion criteria for the intervention phase (offspring): age 8–17; being at ultra high risk for developing a mood or anxiety disorder. Two pathways lead to the qualification of “ultra high risk”: (1) children report elevated symptoms of anxiety or depression, as defined as the 80^th^ percentile of either the subscale Depression or the cluster of subscales of Anxiety on the RCADS self-report. We used data from the large Dutch epidemiological study TRAILS to set these cut-offs at the various age segments (Tracking Adolescents’ Individual Lives [38]). (2) Children meet at least 2 of 3 criteria of our High Risk Index that was developed in the ARIADNE sample: (a) being female, (b) having two affected parents, (c) having a parent with (past) suicidal behaviour.

Exclusion criteria (offspring): mental retardation; not speaking Dutch fluently; severe alcohol or substance use disorder; current diagnosis of a mental disorder that warrants regular treatment. Children with a history of a mental disorder are included, as well as children with a current disorder that had sufficiently been treated (e.g. in the case of stable medication for ADHD).

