#### Randomisation

Since outcome may be dependent on treatment centre and the pathway of inclusion (through elevated symptoms versus no symptoms/HRI only), we decided to work with stratified allocation to treatment condition to ensure a balanced number of participants over conditions. A web-based computer program allows for dynamic on-the-spot randomisation. Randomisation is based on the defined strata as well as on the assigned treatment condition of earlier subjects within the strata. To prevent conscious or unconscious influence on the recruiting team, we choose to conceal the exact details of the randomisation process at this stage (following the recommendations of the CONSORT guidelines [39]). Randomisation takes place after the whole assessment has been completed, so that the first assessment is not dependent on the participant’s knowledge of treatment condition. The research assistant assigns a unique code to each participant. In case one family has several high risk children, the youngest child is entered for randomisation, and the siblings are assigned to the same condition. The research assistant then enters the number of the participant in the web-based randomisation program, and at that moment the computer randomly assigns the treatment condition (active intervention or minimal information; 1:1).

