### Assessments

#### Assessment schedule

Baseline assessment takes place at T0 and comprises questionnaires on the child’s and the parent’s wellbeing (see Table 1). This first screening is used to define the high-risk study population. At T4, all children of parents that were willing to participate will be assessed again with the same measures. The latter is important to evaluate the validity of the initial selection of high risk individuals. If a relatively large proportion of the low-risk group nevertheless has developed a mood or anxiety disorder, this would imply that for future prevention programs the selection strategy should be reconsidered. Selection for the intervention phase is based on the HRI and the RCADS (see Figure 1).

**Table 1 T1:** Assessment schedule for screening (T0) and 24 months follow-up screening

**Measures**	**Child**	**Parent 1**	**Parent 2**
Demographics (+ HRI)		X	
Child anxiety and depression (RCADS)	X	X	
Child impairment (BIS)		X	
Child externalizing symptoms (SNAP)		X	
Parent positive and negative affect (PANAS)		X	X
Optimism (LOT/YLOT)	X	X	X

If a child qualifies for “ultra high risk” based on the screening, he or she may enter the intervention phase of the study. The pre-intervention assessment encompasses structured diagnostic interviews with the child and both parents, as well as a number of relevant other measures (see Table 2). Assessments in the intervention phase are planned for month 0 (T1, at the start of the intervention), month 4 (T2), month 12 (T3), and month 24 (T4). A subset of the instruments is also scheduled for month 6 and 18.

**Table 2 T2:** Assessment schedule for intervention phase

**Measures**	**T1**	**T2**	**T3**	**T4**	**Child**	**Parent1**	**Parent2**
Child diagnoses (DISC)	X	-	X	X	X	X	-
Child anxiety and depression (RCADS)	X	X	X	X	X	X	-
Child impairment (BIS)	X	X	X	X	X	-	-
Child externalizing symptoms (SNAP)	X	X	X	X	X	-	-
Child attachment (IPPA)	X	X	X	X	X	-	-
Implicit child attachment (ABT)	X	-	-	-	-	-	-
Child coping (CSLK)	X	X	X	X	X	-	-
Child attributions (CASQ)	X	X	X	X	X	-	-
Child optimism (YLOT)	X	X	X	X	X	-	-
Child self-esteem (RSES)	X	X	X	X	X	-	-
Expressed emotion (FMSS)	X	-	-	-	-	X	X
Implicit Self-associations (EAST)	X	-	-	-	-	-	-
Child executive functions (BRIEF)	X	-	-	-	-	X	-
Child temperament (EATQ)	X	X	X	X	-	X	-
Parent positive and negative affect (PANAS)	X	X	X	X	-	X	X
Parent depression (BDI)	X	X	X	X	-	X	X
Parent anxiety (BAI)	X	X	X	X	-	X	X

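### The follow-up DISC looks back a fixed 12 months, not to the child's last DISC, so a missed or late interview leaves part of follow-up outside the window; the text should also say that only disorders absent at T1 count as onsets

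*Protocol article*

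**What the plan says.** Under Primary outcome, the protocol article sets the recall period: "At the 12- and 24-follow-up assessments, the interviewer addresses the past 12 months". It continues: "If any disorder was present, the interviewer makes an estimation of the time of onset and the duration of the disorder". The weekly diary helps to date a disorder and judge its duration once DISC criteria are met. It is not a separate way to detect an event.

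In Table 2 (Assessment schedule), the row that begins "Child diagnoses (DISC" is marked at T1, T3 and T4, which are months 0, 12 and 24, and not at T2 (month 4). On the baseline visit the same section says: "The pre-intervention assessment encompasses structured diagnostic interviews with the child and both parents". Under Randomisation: "Randomisation takes place after the whole assessment has been completed".

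Under Participants, one exclusion for offspring is a "current diagnosis of a mental disorder that warrants regular treatment". Children with a past disorder are admitted, "as well as children with a current disorder that had sufficiently been treated". The example given is ADHD on stable medication, but the sentence is not limited to disorders outside the mood and anxiety group.

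**The concern.** The recall window is a fixed length and is not anchored to the previous interview. It fits the schedule only when every interview is held and held on time. Three cases break it:

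- **T3 missed, T4 attended.** The T4 window covers months 12 to 24. A disorder that began and ended in year 1 lies outside it.
- **T3 late.** A T3 at month 14 covers months 2 to 14 and leaves months 0 to 2 out.
- **T4 late.** A T4 at month 26, after a T3 at month 12, covers months 14 to 26 and leaves months 12 to 14 out.

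The number of days with a disorder, a secondary outcome, rests on the same interviews and has the same gap.

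The secondary point is that entry and event use different thresholds. An event is a DISC diagnosis scored by algorithm. Exclusion depends on whether a current disorder warrants regular treatment, and a sufficiently treated current disorder is allowed in. A child could therefore meet DISC mood or anxiety criteria at T1 and be randomised, although not at risk of a new onset of that disorder. The outcome text does not say how such a child is handled. Counted as events, such disorders would occur about equally in both arms and pull the hazard ratio towards 1.

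**Working it through.** **Inputs from Sample size calculation:** control rate 0.11 per person-year; 70% risk reduction, taken as a hazard ratio (HR) of 0.30; one-sided alpha 0.05; power 0.80; 2 years of follow-up; 81 per arm, raised by 25% to 102.

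**The plan's own figure.** Freedman log-rank formula:
- Events needed = (1.645 + 0.842)² × (1.3/0.7)² = 21.3.
- Two-year risks: 1 − exp(−0.22) = 0.1975 (control) and 1 − exp(−0.066) = 0.0639 (intervention).
- n per arm = 21.3 / (0.1975 + 0.0639) = 81.6, against 81 stated.
- 81 × 1.25 = 101.25, rounded up to 102.

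The stated size reproduces.

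**Coverage on schedule.** T3 covers months 0 to 12 and T4 covers months 12 to 24, so none of the 24 months is uncovered.

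**Share of events in year 1.** One-year risks are 1 − exp(−0.11) = 0.1042 and 1 − exp(−0.033) = 0.0325. Then (0.1042 + 0.0325) / (0.1975 + 0.0639) = 0.52.

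**Missed T3.** Let m be the share in each arm who miss T3 but attend T4. The documents give no value for m. The worst case is that none of these children's year-1 onsets is picked up, for example because all have resolved before the T4 window opens. The HR is held at 0.30. Power = Φ(√events × 0.7/1.3 − 1.645).

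| m | Events, 102 per arm | Power, 102 per arm | Power, 81 per arm |
|---|---|---|---|
| 0 | 26.66 | 87.2% | 79.7% |
| 10% | 25.26 | 85.6% | 77.8% |
| 20% | 23.87 | 83.8% | 75.8% |
| 30% | 22.48 | 81.8% | 73.6% |

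**Disorder at T1 wrongly counted as an event.** Let q be the share in each arm, which the documents also do not give. Two-year event risks become 1 − (1 − q)exp(−0.22) and 1 − (1 − q)exp(−0.066). The apparent HR is (0.066 + c)/(0.22 + c), with c = −ln(1 − q). For q = 5%, c = 0.0513 and the HR is 0.1173/0.2713 = 0.43. Power uses the same formula, with the apparent HR and the enlarged event count.

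| q | Apparent HR | Power, 102 per arm | Power, 81 per arm |
|---|---|---|---|
| 0 | 0.30 | 87.2% | 79.7% |
| 2% | 0.36 | 82.8% | 74.7% |
| 5% | 0.43 | 76.3% | 67.7% |
| 10% | 0.53 | 66.3% | 57.8% |

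**The case against.** The strongest objection is that the design has no gap when followed. The 12-month window is used at both follow-up interviews, and together they span the trial. That stands: a reader might infer that first-year onsets are missed by design, and they are not. Loss needs a missed or late interview, and the article gives no rate for either. A year-1 disorder that persists past month 12 would also still fall in the T4 window and could be dated back.

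The parent DISC includes questions on lifetime symptoms, so it cannot be said that year 1 is never asked about. The article does not say at which visits those questions are put, so they do not show that the gap is closed either.

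Other stronger readings also fail:

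- A reader might infer that unasked months are analysed as disorder-free. Statistical analyses names the log-rank test and intention to treat, and does not say how a missed interview is handled. That may be settled in a document not shown.
- A reader might infer that children with a current disorder enrol freely. Disorders that warrant regular treatment are excluded, and the only example of an admitted one is not an endpoint disorder.
- A reader might infer that disorders older than randomisation are counted as onsets. Nothing says so. The T1 DISC and the dating of onset provide the means to tell them apart.

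Finally, longer recall has a price: the article itself doubts that children can place events in time over the past year. That is a fair trade-off, but dating an onset less precisely loses less than leaving the period outside the interview.

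**Conclusion.** The point holds in a limited form. The recall rule as stated does not reach all of follow-up when T3 is missed or when interviews are more than 12 months apart. The likely cost is small: under a worst-case assumption of 10% to 30% missing T3 but attending T4, equal in both arms, power at 102 per arm drops by 1.6 to 5.4 percentage points and stays above 80%.

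The T1 point is an ambiguity in wording, not evidence that prevalent cases are counted. Its effect would be larger if they were: at 5% per arm, the apparent HR would be 0.43 and power 76.3%. Both m and q are assumptions. The planned 81 and 102 per arm are sound on their stated inputs. This is a cheap improvement to the endpoint rules, not a flaw that undermines the trial.

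**What to change.** 1. Replace the fixed window with the whole interval since that child's last completed DISC, for both the child and the parent interview, and use the weekly diary as time anchor. This needs an instruction to interviewers and no new visits. The price is longer recall, with less exact dating, for the few who miss T3.
2. State that only a mood or anxiety disorder absent on the T1 DISC counts as an onset. Define the primary risk set on the T1 DISC and report children with such a disorder at T1 separately. Because T1 is completed before randomisation, this restriction does not break the randomised comparison. The primary set may shrink slightly.

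If the full protocol or analysis plan already holds either rule, it is enough to bring the outcome text into line with it.

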##### Secondary outcomes

As secondary outcomes to our study, we will investigate the number of days with a disorder (based on the DISC-IV), child and parent anxiety and depressive symptoms, quality of life, and cost-effectiveness.

The **Revised Child Anxiety and Depression Scale** (RCADS; RCADS; [43]) is a 47-item self-report and a parent-report questionnaire, with scales corresponding to separation anxiety disorder, social phobia, generalized anxiety disorder, panic disorder, obsessive-compulsive disorder and major depressive disorder.

The **Inventory of Depressive Symptomatology** IDS; [44] is a 30-item measure of depressive signs and symptoms in adults. In the current study the Dutch translation of the self-report (SR) version was used to assess current depressive symptoms of the parents

The **Beck Anxiety Inventory** BAI; [45] is a 21-item self-report instrument that assesses the overall severity of anxiety in adults. In this study the BAI is used to assess current anxiety symptoms of parents.

To assess quality of life, we included the EuroQol (**EQ-5D**[46]), being a brief, easy to administer questionnaire comprised of 2 components: a description of the respondent’s own health using a health status classification system with 5 items and a rating of “own health” by means of a visual analogue scale (VAS; 0–100). We included a child version, a parent version and a regular adult self-report in the current study.

Information on healthcare consumption will be registered with a comprehensive questionnaire capturing (mental) healthcare consumption and other illness-related economic consequences for society. The instrument is administered to the parents and assesses various cost aspects of the child and each parent, including contacts with healthcare professionals, informal care and absence from school or work. The instrument is a revision and adjustment of the youth care version of the TIC-p [47] and has been adopted to the specific situation of the current study. The intervention costs are also monitored including therapist time spent on the actual intervention, the preparation of sessions, course material, travelling costs, and the costs of the training of the therapists.

##### Mediators and moderators of change

To examine potential mediators and moderators of change we assessed the following measures focused on child characteristics and parent characteristics:

Measures on the child’s characteristics

The **Youth Life Orientation (YLOT;**[48]**)** is a 12-item measure of dispositional optimism and pessimism that was developed as a child analogue of the widely used Life Orientation Test.

The **Children’s Attributional Style Questionnaire - Revised** CASQ-R; [49] is a 24-item shortened measure designed to assess children’s causal explanations for positive and negative events.

The **Rosenberg Self-Esteem Scale** RSES; [50] is developed as a 15-item self-esteem scale for children and adults and translated into different languages.

An Extrinsic Affective Simon Task **(EAS**T; [51]) is a computerized reaction time task to indirectly measure attitudes. The current EAST was designed for this study and intends to assess the strength of the children’s automatic associations between themselves and sad (or happy) mood, as well as anxious (or calm) feelings. It is a categorization task, during which target words like “myself”, “them”, “anxious”, or “table” appear in the middle of the computer screen, and children have to assign the target words to one of the target labels (me, not-me, feeling, or object) that are set at either the left or the right side of the screen. In correspondence, children press a right or left response key as quickly as possible. The underlying principle is that a person will be faster in categorizing anxiety or depression words to the key that is defined as both “feeling” and “me” label if the person regards him or herself as anxious or depressed. In contrast, the person may be slower in categorizing the words related to calmth or happiness to a key that is defined as both a “feeling” and “me” label. These types of automatic anxious- and depressed self-associations have been found to be predictive of symptomatology in adults [37].

The **Coping Strategies Checklist for Children** CCSC-R1; Dutch version: CSLK; [52,53] contains 14 subscales, including a variety of cognitive coping strategies. Earlier research in offspring has shown that it may be important to distinguish between coping at home and coping elsewhere [28]. Therefore, we administered two versions of the coping questionnaire. The scale contains five coping dimensions (Seeking understanding, Control, Optimism, Wishful thinking, Support for feeling and Support for actions).

The **Brief Impairment Scale** BIS; [54] is a multidimensional scale of functional impairment for children and adolescents. The BIS is a 23-item instrument that evaluates three domains of functioning: interpersonal relations, school/work functioning, and self-care/self-fulfillment.

The **Behaviour Rating of Executive Functioning** BRIEF; [55] is a 86-item standardized rating scale used to assess children’s executive functions in home and school environments. The **Early Adolescent Temperament Questionnaire – Revised version** (EATQ-R; [56]) is a parent-report questionnaire that was developed to measure child temperamental aspects associated with self-regulation. Three factors were included in the present study with a total of 44 items, namely Effortful control (including activation control, attentional control, and inhibitory control), Negative affect (including Fear, Frustration, and Shyness) and High intensity pleasure/Surgency.

The **SNAP-IV Parent Rating Scale** (SNAP; [57]) is a parent report questionnaire including 18 items for ADHD (inattention and hyperactivity/impulsivity) and 8 items for ODD symptoms.

The Dutch version of the **Inventory of Parent and Peer Attachment** IPPA; [58,59] is an 11-item self-report instrument that is used to assess attachment to each parent and one significant other.

Mother-child attachment was also administered through a computer task, the **Attentional Breadth Task**[60], that was programmed in e-prime. The task is based on the assumption that information processing may be distorted in individuals with insecure attachment when it comes to attachment-relevant information. Insecurely attached children may be more alert to stimuli that are related to the mother, and may be more likely to have a smaller attention span when the mother is involved. During the task, children are shown a picture of either their mother or an unfamiliar woman, as well as a dark dot that appears either close to the picture or further away. Children have to report on whether the woman was their mother or the unfamiliar woman, and must then identify where the dot appeared. For further details and specifications, see [60]. Attentional Narrowing Indices (ANI) are presumed to be a proxy for implicit attachment security and can be derived from the child’s reaction times (ANI = stimulus close to picture – stimulus far from picture).

The **Five Minute Speech Sample**[61] is used to assess perceived expressed emotion by the father and the mother. Each parent is asked to talk for five minutes about his or her child and the relationship they have with their child. After coding the text, two components can be derived: criticism (CRIT) and emotional overinvolvement (EOI).

##### Measures on parental well-being and psychopathology

The WMH Survey version of the World Health Organization (WHO) **Composite International Diagnostic Interview** WMH-CIDI, now CIDI 3.0; [62] is a comprehensive, fully-structured interview designed to be used by trained lay interviewers for the assessment of mental disorders according to the definitions and criteria of DSM-IV [41]. We used the Dutch translation [63] in a computerized version, containing of the following sections: Depression, Mania, Panic Disorder, Social Phobia, Separation Anxiety Disorder, Specific Phobia, Generalized Anxiety Disorder, Obsessive Compulsive Disorder.

The **Alcohol Use Disorders Identification Test**[64,65] was developed by the World Health Organization (WHO) as a simple method of screening for excessive drinking. Seven of its items reflect harmful and dependent drinking, while three items assess alcohol consumption behaviour in terms of quantity and frequency of drinking.

The **Positive and Negative Affect Schedule** (PANAS) is a 20-item self-report measure of positive and negative affect [66]. Negative Affect and Positive Affect reflect dispositional dimensions, with high NA epitomized by subjective distress and unpleasurable engagement, and low NA by the absence of these feelings. By contrast, PA represents the extent to which an adults experiences pleasurable engagement with the environment.

